|                                                 | 
6. Register-based search for health economic effects on all levels of care (primary, specialized) and society (sick leave).
 
7. The difference in kinematic output between measurement systems (i.e., multi-sensor and mobile app) during the tests specified in 2a and 2b.
 
8. The reliability and validity of the Swedish VSS-SF translation.
 
9. The frequency (percentage) of participants with:
BPPV at 3 months after AVS onset;
symptoms indicating BPPV 6 weeks after an AVS using a BPPV specific questionnaire;
positional nystagmus (non-BPPV) 3 months after an AVS;
positional vertigo (non-BPPV) 3 months after an AVS;
BPPV in the treatment vs control group; and
the DHI/VSS-SF/steps/safety results differences between the BPPV, suspected BPPV and non-BPPV groups.
 
Safety endpoint:
The proportion of participants who has experienced falls/fractures since study start up until 6 weeks, 3 months and 12 months; and the number of falls/fractures in each study arm at the same time points.
 |
| Planned duration of the clinical investigation: | October 2021 –December 2024                                                                                                                                                                                                                                                                                                                                                                                                                                                                                                                                                                                                                                                                                                                                                                                                                                                                                                                                                                                                                                                             |

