| 9. Investigate the frequency of benign positional paroxysmal vertigo (BPPV) after AVS at different time point and using different evaluation methods; investigate the correlation between BPPV and the DHI, VSS-SF, steps and safety endpoints; and investigate the effect of treatment arm allocation on the risk for BPPV. | 9. The frequency (percentage) of participants with:
BPPV at 3 months after AVS onset; symptoms indicating BPPV 6 weeks after an AVS using a BPPV specific questionnaire;
positional nystagmus (non-BPPV) 3 months after an AVS; positional vertigo (non-BPPV) 3 months after an AVS;
BPPV in the treatment vs control group; and the DHI/VSS-SF/steps/safety results differences between the BPPV, suspected BPPV and non-BPPV groups. |
| Safety objective                                                                                                                                                                                                                                                                                                      | Safety endpoint                                                                                                                                                                                                                                                                                                                                                                                                                          |
| Compare the effects on the risk of falls and fractures and any other of online vestibular rehabilitation compared with standard written instructions.                                                                                                                                                                        | The proportion of participants who has experienced falls/fractures since study start up until 6 weeks, 3 months and 12 months; and the number of falls/fractures in each study arm at the same time points.                                                                                                                                                                                                                                     |

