weekly online sessions consist of educational texts, symptom control techniques, scoring tests and exercise prescriptions for the following week. The exercises for the following week after each online session will be adapted to the user and thus become successively more difficult if the user scores lower discomfort during evaluations, or the opposite if the user scores higher discomfort. There are 6 different exercises in the tool: 1. Head shake with open eyes, gaze following the head; 2. Head nod with open eyes, gaze following the head; 3. Head shake with closed eyes; 4. Head nod with closed eyes; 5. Head shake with open eyes, gaze fixated and; 6. Head nod with open eyes, gaze fixated. These exercises are performed sitting, standing and walking depending on symptom intensity. There are 4 symptom control techniques in the tool in order to deal with secondary anxiety issues related to the vertigo: 1. Controlled breathing; 2. Relaxation; 3. Stress management and; 4. Thought control.

Control: After randomization written instructions with the 6 different exercises from the online rehabilitation tool is handed out and the participant is instructed to increase difficulty if possible. Participants are also given general advice to prevent inactivity and secondary dizziness and fear of motion. Data collection as for the intervention arm. At the end of the core study at 3 months from randomization the standard care study arm participants will also be granted access to the online rehabilitation tool and followed until 12 months.

The Swedish translations of VSS-SF, DHI, and EQ-5D-3L are collected locally at all sites by the site study coordinator. These questionnaire data will be collected by in-person interview at day 0, week 6 and after 3 months, except for VSS-SF at 6 weeks (primary endpoint) which will be collected by phone call interview by a blinded study coordinator at either the same site or a different site. In the case of the first 100 included subjects, the VSS-SF at 6 weeks (primary endpoint) will be collected by phone call interview twice, 48 hours apart, as part of the statistical validation of the Swedish translation of the VSS-SF questionnaire. Also, at week 3 and after 12 months VSS-SF and EQ-5D data will be collected by phone call interview (figure 1).

The T25-FW data will be collected by letting the subject walk a clearly marked 25-foot course during follow-up appointments at each site.

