Basic body sway data will be collected by each site study coordinator using a locally developed application which utilizes cell phone built-in motion tracking. An enhanced gait analysis with a wearable motion tracking system will be performed at Umeå University Hospital for in-depth measurements.

The participants will be instructed to keep a provided pedometer on them as often as possible during the first 3 months. The total number of steps for the first 6 weeks, and from week 6 to 3 months will be recorded into REDCap will be compared between the study arms at week 6 and after 3 months.

At sites with access to vHIT we will also measure VOR gain and catch-up saccades by performing vHIT at day 0, 6 weeks and 3 months.

The catch-up saccades (yes/no, proportion of impulses with saccades) will also be compared between the study arms at 6 weeks and 3 months (affected side).

The 12 months data collection to capture potential long-term effects of early intervention will be performed by the Umeå University Hospital study coordinator by contacting all participants by telephone at 12 months after inclusion. During this phone call one last round of VSS-SF questionnaire data will be collected (Figure 1).

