**Table 1. Schedule of events**

| Visit/contact                       | Baseline | 3 weeks
(by phone) | 6 weeks | 3 months | 12 months (by
phone) | Comments                                            |
|-------------------------------------|----------|-----------------------|---------|----------|-------------------------|-----------------------------------------------------|
| Target day                          | 0        | 21 +/-3               | 42 +/-3 | 90 +/-7  | 360 +/-14               |                                                     |
| Eligibility
screening, history   | x        |                       |         |          |                         |                                                     |
| Randomization                       | x        |                       |         |          |                         |                                                     |
| VSS-SF                              | x        | x                     | x       | x        | x                       | Primary endpoint @6
weeks                        |
| EQ-5D                               | x        |                       | x       | x        | x                       |                                                     |
| DHI                                 | x        |                       | x       | x        |                         |                                                     |
| T25-FW                              | x        |                       | x       | x        |                         |                                                     |
| Body sway                           | x        |                       | x       | x        |                         |                                                     |
| Enhanced body
sway analyses      | x        |                       | x       | x        |                         | At selected sites only                              |
| vHIT                                | x        |                       | x       | x        |                         | At selected sites only                              |
| Steps, falls and
fractures       |          |                       | x       | x        |                         | Total steps, since
enrollment or last visit      |
| BPPV questions                      |          |                       | x       | x        |                         |                                                     |

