| BPPV testing                        |          |                       |         | x        |                         |                                                     |
| Compliance                          |          | x                     | x       |          |                         | Questionnaire data,
number of weekly
sessions |
| Trial termination
form (local)   |          |                       |         | x        |                         | Last site visit @ 3
months                       |
| Trial termination
form (central) |          |                       |         |          | x                       |                                                     |
| Estimated time
requirement       | 150 min  | 15 min                | 120 min | 120 min  | 15 min                  | Total 7 hours per
participant                    |

Abbreviations: VSS-SF = vertigo symptom scale short form; EQ-5D = EuroQol five-dimension scale; DHI = dizziness handicap inventory; T25-FW = timed 25-foot walk test; SD = standard deviation; vHIT = video head impulse test.

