## 8.2. Recording and Reporting

### 8.2.1. Recording

The PI or an authorized designee will record in the eCRF:

- all AEs except the events below specified not to be recorded:
  - Vertigo, nausea or mild discomfort during the vestibular rehabilitation, regardless of randomization allocation. These symptoms are common after acute vertigo and during vestibular rehabilitation and all subjects are expected to develop such symptoms.
  - Falls and fractures are recorded and reported as stand-alone endpoints and therefore not included in the AE reporting.
  - VSS-SF (Vertigo Symptom Scale - Short Form) measures the frequency of 15 known vestibular symptoms and these are recorded and reported as endpoints and therefore not included in the AE reporting.
- all SAEs
- all DDs
- any new finding in relation to any of the above-mentioned events.

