| Proportion with catch-up saccades                                               | Participants at sites with access to vHIT | 50+50                                                  | Unknown                                                  | Unknown | Binary logistic regression |

|                                                                                                |                        |       |                         |         |                            |
|------------------------------------------------------------------------------------------------|------------------------|-------|-------------------------|---------|----------------------------|
| on vHIT (affected side) @w6 and @m3                                                            |                        |       |                         |         |                            |
| Body sway until m3                                                                             | All participants       | 92+92 | Unknown                 | Unknown | Mixed models               |
| Enhanced body sway analysis (gait analysis) until m3                                           | Umeå participants only | 25+25 | Unknown                 | Unknown | Mixed models               |
| Total steps since last visit @w6 and @m3.                                                      | All participants       | 92+92 | Unknown                 | Unknown | ANCOVA                     |
| Self-reported vestibular rehabilitation compliance until 6w (mean number of training sessions) | All participants       | 92+92 | Unknown                 | Unknown | Mixed models               |
| Proportion with falls or fractures                                                             | All participants       | 92+92 | Unknown                 | Unknown | Binary logistic regression |
| Proportion with BPPV                                                                           | All participants       | 184   | Estimated frequency 10% | N/A     | Binary logistic regression |

Abbreviations: VSS-SF = vertigo symptom scale short form; EQ-5D = EuroQol five-dimension scale; DHI = dizziness handicap inventory; T25-FW = timed 25-foot walk test; SD = standard deviation; vHIT = video head impulse test; @w6 = at 6 weeks; @m3 = at 3 months; @m12 = at 12 months.

\*Power calculations based on mean gain differences before and after vestibular rehabilitation

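### The falls and fractures safety endpoint runs to 12 months, but Table 1 and section 6.7 schedule no collection after 3 months, and section 8.2.1 removes the adverse-event record that could have filled the gap

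*Protocol*

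**What the plan says.** The safety endpoint in section 5.2 is "The proportion of participants who has experienced falls/fractures since study start up until 6 weeks, 3 months and 12 months", together with the number of events per arm at the same time points. The synopsis repeats the horizon: "since study start up until 6 weeks, 3 months and 12 months".

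Section 8.2.1 tells sites to record all adverse events apart from a short list. Falls and fractures are on that list, for this reason: "Falls and fractures are recorded and reported as stand-alone endpoints and therefore not included in the AE reporting". All serious adverse events stay recordable.

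In Table 1 the row that begins "Steps, falls and" is marked at 6 weeks and 3 months, and its 12-month cell is blank. The local termination form carries a comment that begins "Last site visit @ 3" (months), so the only later contact is the 12-month phone call. Section 6.7 describes that call twice: "Also, at week 3 and after 12 months VSS-SF and EQ-5D data will be collected by phone call interview", and "During this phone call one last round of VSS-SF questionnaire data will be collected". Neither sentence mentions falls or fractures.

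Table 2 lists the analysis as "Proportion with falls or fractures", by binary logistic regression, with no time point. The register search in the synopsis is stated for health-economic effects and is not linked to this endpoint. Sections 4.1, 6.1 and 6.7 give the control arm access to the online tool at 3 months.

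**The concern.** The exemption in section 8.2.1 is a reasonable choice if the endpoint record really takes the place of the adverse-event record. Up to 3 months it does. After 3 months the visible text schedules no endpoint record, yet the exemption stays in force. A non-serious fall or fracture in that period then has no place in the plan where it is due to be written down.

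Two things are at stake. First, one of the three stated time points of the trial's only safety endpoint cannot be delivered from the schedule as written. A 12-month figure would rest on events to 3 months plus whatever later events were serious. Second, controls first use the device at 3 months, so no scheduled falls collection covers any of their time on it.

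**Working it through.** This is a cross-check of the text. The only arithmetic is the length of the gap.

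**Inputs**
- Endpoint time points: 6 weeks, 3 months, 12 months (synopsis; section 5.2).
- Target days in Table 1: 42 ± 3, 90 ± 7, 360 ± 14.
- Falls and fractures row in Table 1: marked at day 42 and day 90.
- Content of the 12-month call: VSS-SF and EQ-5D (section 6.7; the same two marks in Table 1), plus the central termination form (Table 1).
- Access to the tool: day 0 for the intervention arm, 3 months for controls.

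**Endpoint against schedule**

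| Time point | In the endpoint | Falls and fractures marked in Table 1 | Adverse-event record if non-serious | Adverse-event record if serious |
|---|---|---|---|---|
| 6 weeks | yes | yes | no (8.2.1) | yes |
| 3 months | yes | yes | no (8.2.1) | yes |
| 12 months | yes | no | no (8.2.1) | yes |

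One of three stated time points has no scheduled collection. The blank is unlikely to be a layout effect, because VSS-SF and EQ-5D are marked in the same 12-month column.

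**Length of the gap**
- At target days: 360 − 90 = 270 days, and 270 / 360 = 75% of follow-up.
- Shortest within the visit windows: (360 − 14) − (90 + 7) = 249 days.
- Longest within the visit windows: (360 + 14) − (90 − 7) = 291 days.

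**Scheduled falls collections after device use begins**
- Intervention arm: 2 (day 42 and day 90).
- Control arm: 0.

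**Direction of the error**

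The 12-month endpoint is cumulative from study start. If nothing non-serious is collected after day 90, each participant's count at 12 months equals the count at 3 months plus later serious events. The total is therefore too low in both arms by the number of non-serious events after day 90. The protocol gives no fall rate, so the size of that shortfall cannot be derived from it.

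**The case against.** The strongest reply is that an item missing from Table 1 or section 6.7 does not prove that it is not collected. The two sources do not fully agree with each other. Section 6.7 places EQ-5D at week 3, where Table 1 has no mark, and one of its two sentences on the 12-month call mentions VSS-SF alone. Figure 1, which section 6.7 cites for these calls, is not visible, and neither is the eCRF. The endpoint states 12 months twice, so a mark left out of Table 1 is a plausible explanation. This stands, and it limits the claim to a conflict between endpoint and schedule. It does not remove the need to correct the text, because sites work from the schedule.

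A second reply is that the randomised contrast of tool against leaflet ends at 3 months, when controls gain access, and both collections inside it are scheduled. This also stands: the comparison that matters most for safety is intact. The share of days without collection should not be read as a share of lost information.

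A reader might also infer that the exemption leaves falls without any assessment of relatedness, and so cuts off site follow-up. The documents do not support that as a finding. An endpoint defined as a proportion and a count does not show which fields the form holds. The site follow-up in section 8.4 applies to serious events and device-related events still ongoing at study end, which few non-serious falls would be. Widening section 8.2.1 to bring possibly related falls back as adverse events is a matter of preference. It would add attribution by people who know the allocation, and any wording about serious events would repeat what the section already requires.

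**Conclusion.** The point holds as an internal conflict. The only safety endpoint is stated to 12 months, while Table 1 and section 6.7 schedule its collection to 3 months. Because of section 8.2.1, non-serious falls and fractures in the remaining 270 of 360 days have no scheduled record in the visible text. That period covers all of the control arm's device use. A 12-month figure produced from the plan as written would be too low, by an amount the protocol does not allow one to estimate.

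Two stronger conclusions would go too far. The text does not show that 12-month falls are certainly uncollected, since the eCRF and Figure 1 are unseen. Nor does it show that serious falls escape, since all serious adverse events are recorded. The primary endpoint and the 6-week and 3-month safety comparisons are not touched. The matter should be corrected because the time point is a stated endpoint and the remedy is small.

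**What to change.** 1. In Table 1, mark falls and fractures at the existing 12-month phone call.
2. In section 6.7, name them in the description of that call: number and date of each event since the 3-month visit.
3. Report participants who passed the 12-month call before the change as not collected, not as free of events. Section 9.6 gives 138 included by April 2023, so some may already be past it; the protocol does not say how many.
4. Label the 12-month comparison as early versus delayed access, because both arms have the tool after 3 months.

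If the eCRF already asks about falls and fractures at 12 months, only Table 1 and section 6.7 need correcting, and step 3 falls away for participants who were asked.

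The cost is a few extra questions on a call that already takes place, with no new visit. The main weakness is recall over about nine months (270 days), which will miss minor falls, so the 12-month count should be presented with that limit. As an optional addition, the same questions could ask whether the event happened during an exercise; the correction does not depend on it.

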### 8.2.2. Reporting

The investigators will report to the sponsor, immediately but not later than 3 calendar days after investigation site study personnel's awareness of the event. The investigators will use the eCRF AE/SAE form for reporting events to the Sponsor.

The sponsor will report, to the Swedish Medical Products Agency (Läkemedelsverket), all of the following:

- any SAE that has a causal relationship with the investigational device or the investigation procedure, or where such causal relationship is reasonably possible.

- any DD that might have led to a SAE if appropriate action had not been taken, intervention had not occurred, or circumstances had been less fortunate; and
- any new findings in relation to any event referred to above.

Reporting by the sponsor will be done by filling out the “Summary Reporting Form” (MDCG 2020-10/1). The form will be filled in/updated for each reportable event or for new findings/updates to already reported events. For events that indicate an imminent risk of death, serious injury, or serious illness and that requires prompt remedial action for other patients/subjects, users or other persons or a new finding to it will be reported immediately, but not later than 2 calendar days after awareness by sponsor of a new reportable event or of new information in relation with an already reported event. Any other reportable events or a new finding/update to it will be reported immediately, but not later than 7 calendar days following the date of awareness by the sponsor of the new reportable event or of new information in relation with an already reported event.

